### Intervention

Eligible participants would randomly be assigned to either the treatment or control group. Participants in control group would receive treatment as usual (TAU) which comprise of two weekly in-person physiotherapy sessions and two sessions with a medical doctor at the University of Ghana Hospital Participants in the control group would receive upper and lower limb physical rehabilitation and undergo medical review (medication review and symptom management) with medical doctors.

Participants in the intervention group would receive comprehensive nursing neurorehabilitation support in addition to existing service at the hospital (treatment as usual). The components of the intervention are guided by relevant literature, established guidelines [29–31] and have been reviewed by a panel of experts including two neuroscience nurses, two community health nurses, three neurologists, one stroke specialist, one physiotherapist and a stroke survivor. Patients would undergo assessment and receive various therapies in appropriate domains for 6months. A follow-up evaluation would be performed at the end, 30- and 90-days after the intervention (S2 Fig). The intervention would involve the following components;

#### Initial and ongoing patient assessment

Participants would undergo various assessments on motor function, cognitive capacity, anxiety and depressive levels and nutritional status utilizing evidenced-based assessment tools. The initial assessment would span in the first week of the intervention. Based on the problems and needs identified during the assessment, participants would receive a bundle of interventions in the domains of cognitive rehabilitation, physical rehabilitation, emotional support, and stroke education. These interventions would be provided twice a week in 1hr-to-1hr 30mins per session via video calls on WhatsApp or phone calls. These calls would be scheduled weekly with the participants after needs and availability assessment to improve response. Participants with close-by caregivers would be asked to provide the contacts of their caregivers as back-up. A participant in the intervention may have 192 sessions maximum or 48 sessions minimum in the span of the intervention.

#### Cognitive rehabilitation domain

This domain is mainly focuses on supporting participants to establish a daily routine, improving memory and attention and mitigating spatial neglect [32]. We would guide participants in clearly structuring their daily activities based on their preferences and setting priorities [9]. Participants also be guided in visual scanning activities, attention training exercises and utilizing memory aids [33].

#### Physical rehabilitation domain

The aim of physical rehabilitation will be the recovery of the patient’s motor functioning impacted by stroke [8]. Participants would undergo stroke-specific impairment assessment using the Fugl-Meyer Assessment (FMA) [34]. Based on identified needs the participant would undergo graded physical therapy including passive and activities range of motion exercises, constraint-induced exercises, and stress ball usage with the support of their caregivers. Caregivers would be provided education on how to support participants through the therapy, and handle equipment such as stress ball. Additionally, participants and their caregivers would be educated on proper use of assistive devices for gait and mobility training.

#### Emotional support

This domain is geared towards assessing and supporting the emotional status of participants and their caregivers. We would provide counselling sessions to help identify the extent of loss which greatly influences the emotional status and recovery of participants [35]. Additionally, study participants would be guided in recognizing their own emotions and identifying personalized but effective coping strategies [9].

#### Stroke education

Education lasting from 30 to 60mins based on participant’s and caregiver’s learning needs would be provided for participants and their relatives per session. The target of the information provided would focus on improving the participant’s understanding of the disease condition, modifiable risk factors of recurrence, pain management, preventing pressure ulcers, oral and catheter care, continence management, the importance of following professional dietary recommendations, and healthy nutrition in the recovery process [36].

See (Table 1) for details regarding the intervention presented based on the TiDieR checklist.

**Table 1 pone.0280973.t001:** Details of intervention.

Component of the intervention	What (procedures)	Who	How (mode of delivery)	Where (location of intervention)	When (schedule), How much, dose, intensity	Tailoring
Initial comprehensive assessment	Patient’s baseline assessment on: Motor functioning Cognitive capacity Levels of anxiety & depression	Stroke nurses, and physiotherapist and neuropsychologist as consultants.	Individual one-on-one Calls via cell phones video calls	Patient’s home Rehab center	Only once as this serves as the baseline assessment.	All participants would undergo this initial assessment for identification problem.
Ongoing assessment	Identifying patient’s needs priority areas progress and possible deterioration motor functioning cognitive capacity levels of anxiety and depression	Stroke nurses	Individual one-on-one Calls via cell phones video calls	Patient’s home	Bi-Weekly Every other week Monthly As needed	Individualized
Cognitive rehabilitation domain	Guiding patients to establish a structured routine. Attention training exercises. learning the proper use of memory aids	Stroke nurses	Individual one-on-one calls via cell phones. video calls	Patient’s homes	Every other week A total of 12 sessions throughout the project	Based on cognitive needs participants may be guided in using different strategies to: improve memory and attention. mitigate spatial neglect
Physical rehabilitation domain	Passive and/or active range of motion exercises constraint induced therapy and stress-ball usage. Education on proper usage of assistive devices would also be provided	Stroke nurses, physiotherapist	Individual one-on-one Calls via cell phones video call	Patient’s homes	Twice a week. A maximum of 48 sessions throughout the project.	Physical domains sessions are tailored to the functional needs of participants. Based on physical needs, intervention may be guided in using different strategies to: Aid those who can walk and stand with aids. Those who cannot walk but stand with some gait issues. And those who cannot stand at all
Emotional support domain	Understanding the extent of loss Recognizing emotions and mood changes Identifying personalized coping strategies	Stroke nurses	Individual one-on-one calls via cell phones Video calls	Patient’s homes	Biweekly A maximum of 12 sessions throughout the project	Participants would have to the opportunity to identify individual coping strategies.
Stroke education domain	modifiable risk factors pain management pressure ulcer prevention nutrition and continence.	Stroke nurses	Individual one-on-one Calls via cell phones Video calls Group sessions	Patient’s homes	Every three weeks during the intervention period.	Certain education topics would be provided on one-on-one and based on patient needs whereas topics on modifiable risk factors and nutrition may be provided in group sessions

### Outcomes and outcome measures

#### Primary outcomes

Based on the CONSORT checklist [37] the pilot study is primarily aimed at assessing the preliminary feasibility and acceptability of the intervention in the Ghanaian context.

*Feasibility*. Feasibility would be measured by retention rate, rate of adverse events and recording the details of resources used in implementing the intervention. Additionally, duration of sessions and cost of internet for the research team and study participants would be captured.

*Participant satisfaction*. This will include the use of a 12-item Patient Satisfaction with Telehealth questionnaire to assess the level of satisfaction of participants on delivery of the intervention, time spent, quality of audio-visual channels involved and overall perceived benefits [38].

Factors influencing user satisfaction: Qualitative data of participant experiences and in-depth factors that influence their rate level of satisfaction would be captured in order to provide in-depth explanation of satisfaction levels. This would be guided by an interview probe designed for purpose.

#### Secondary outcome

*Self-efficacy*. The secondary and clinical outcome in focus would be Stroke Self-efficacy. The goal is assessed potential effectiveness of the intervention in improving self-efficacy among patients. This would be measured the Stroke Self Efficacy Questionnaire (SSEQ). The SSEQ is a 13-item scalar questionnaire that measures the stroke survivor’s ability and confidence in performing tasks under self-care, mobility and effective coping. The scale is also vital for assessing the functional performance of the study participants after the intervention [39, 40]. This tool is most appropriate because it has been proven to have good face validity with a Cronbach Alpha of 0.90 suggesting good internal consistency and higher criterion validity when compared with other self-efficacy scales [41].

### Proposed sample size

We aim at recruiting 20 participants per group (total = 40 participants). The size however is guided by Julious’ rule of thumb for 12 participants per group in pilot trial [42]. The potential attrition rate estimated is 20% per group. During the follow-up phase, qualitative data on participant experiences through one-on-one interviews would be captured from 15 conveniently sampled participants from the intervention group. According to Hennick and Kaisser [43] a 15 sample is appropriate for reaching data saturation. An interview guide designed for purpose who be used to gather needed data.

### Data collection, entry and management

Data would be gathered from participants before the intervention but after recruitment and after the intervention. Baseline data would be gathered on two occasions prior to the intervention. Before randomization, data on participant demographic characteristics, patient history, functional status, psychological functioning and cognitive capacity would be gathered. Baseline data on patient’s self-efficacy would be collected before the first session of the intervention via phone survey. The second phase of data collection would take place immediately after the end intervention capturing quantitative date on user satisfaction, qualitative data on experiences throughout the intervention only for participants in the intervention group and stroke-self efficacy levels for participants in both group. The third and final phase of data collection would be executed 4 weeks and 12 weeks after the intervention respectively capturing stroke efficacy levels in both groups. The data collection process would be undertaken by an independent assessor who are unaware of participant allocation. After completing each phase of data collection, the quantitative data would be entered into a spreadsheet using Microsoft Excel. The data would be processed for outliers and missing inputs. Qualitative interviews would be audiotaped, audios would be saved in a PC folder and later transcribed for analysis. The entered information and saved audios would be protected by a password only accessible by the research team.

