### Randomization, allocation and blinding

After eligible participants have provided informed consent and undergone baseline screening, they would be randomly assigned to the intervention group (Nurse-led rehabilitation support + Treatment as usual) and control group (only treatment as usual).

Randomization would be conducted by an independent researcher who is not involved in the study. She will use a combination of block and stratified randomization to assign 40 participants to either the intervention group or the control group. Prior to the assignment, participants would be stratified based on the type of stroke (hemorrhagic vs ischemic). Within each stratum, participants will be assigned using block randomization with block size of four. Additionally, the independent researcher would generate random sequence for the block order with an online random sequence generator (sealedenvelope.com). The sequence numbers would be written and placed in opaque envelopes by the independent researcher. Immediately a participant signs the consent form, the principal investigator ([name]) would inform to sequentially open the envelope in the corresponding block and assign participant to the group indicated in the envelope.

Participants will not be blinded to the assigned group. Also, It will not be possible to blind the interventionists (stroke nurses and other health professionals) providing the intervention in this study. Essentially both parties (participants and interventionists would be unmasked. However, the assessors of study outcomes would be blinded to the allocation of participants. Also, assessors gathering baseline data on self-efficacy and any other data after group allocation would be blinded to the allocation status of participants.

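### Assessor blinding is claimed for all data gathered after allocation, but the post-intervention round includes intervention-arm-only data that reveal allocation

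*Protocol article*

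**What the plan says.** Two sections of the protocol article promise blinded assessment, and neither makes an exception.

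- *Randomization, allocation and blinding* says that "the assessors of study outcomes would be blinded to the allocation of participants". It then widens the promise: "assessors gathering baseline data on self-efficacy and any other data after group allocation would be blinded to the allocation status of participants". The same section says that participants and those who deliver the intervention are not masked.
- *Data collection, entry and management* covers the whole process in one sentence: "The data collection process would be undertaken by an independent assessor who are unaware of participant allocation".

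The second of these sections also lists what each round contains. On the first round after treatment: "The second phase of data collection would take place immediately after the end intervention capturing quantitative date on user satisfaction". The sentence goes on to list "qualitative data on experiences throughout the intervention only for participants in the intervention group and stroke-self efficacy levels for participants in both group". The later rounds, which again cover the two arms, are described thus: "The third and final phase of data collection would be executed 4 weeks and 12 weeks after the intervention respectively capturing stroke efficacy levels in" (the sentence then names the arms).

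*Primary outcomes* names the satisfaction instrument as a "12-item Patient Satisfaction with Telehealth questionnaire to assess the level of satisfaction of participants on delivery of the intervention". *Proposed sample size* adds that "qualitative data on participant experiences through one-on-one interviews would be captured from 15 conveniently sampled participants from the intervention group", and places this in the follow-up phase.

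**The concern.** A person cannot give an instrument to one arm only and remain unaware of who is in that arm. The blinding promise and the list of tasks in the first post-treatment round therefore conflict.

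What is at stake is the between-arm comparison of the SSEQ, the one clinical outcome that the article names. *Data analysis* tests it between groups at each follow-up at a two-sided 0.05 level, and the abstract says that the findings are meant for use in a larger study. With participants and interventionists unmasked, blinding of the assessor is the only masking that the trial claims. An interviewer who knows the arm could prompt or encourage differently when taking the SSEQ. The results could also be reported as assessor-blinded when they were not, and a larger trial could inherit the same arrangement.

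**Working it through.** The point is about procedure and rests on no power or sample-size figure. The check is to set the statements side by side; the arithmetic only gives scale.

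**1. Which data does the blinding claim cover?** All data after allocation (*Randomization, allocation and blinding*) and the whole collection process (*Data collection, entry and management*). No round and no instrument is exempted.

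**2. Which data in the first post-treatment round reveal the arm?**
- Experience data: explicitly from the intervention group only.
- Satisfaction: the instrument asks about delivery of the intervention and audio-visual quality. Under *Intervention*, controls receive in-person physiotherapy and medical review only, so the questionnaire has no content for them.
- SSEQ: both groups, so it reveals nothing by itself.

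**3. Can 1 and 2 both hold?** No. The first two items cannot be collected by someone who does not know the arm.

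**4. Which SSEQ rounds are affected?** There are three after treatment: immediate, 4 weeks and 12 weeks.
- Immediate: affected unless the SSEQ is completed before the arm-specific instruments. The article gives no order.
- 4 and 12 weeks (2 of 3 rounds): affected if the person who collected the arm-specific data also takes these SSEQs. The article names no one else.
- Baseline SSEQ: taken before the first session, so not affected by this route.

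**5. How many participants are revealed?** Inputs from *Proposed sample size*: 20 per arm, 20% attrition, 15 interviewed. The article does not say when attrition occurs, so the number per arm at the first follow-up lies between 20 × (1 − 0.20) = 16 and 20.
- If the assessor administers the satisfaction questionnaire: all 16 to 20 intervention participants are revealed, and the controls by elimination.
- If only the interviews reveal the arm: 15/20 = 75% to 15/16 = 94% of the intervention arm. Among those not interviewed, controls make up 20/(20 + 5) = 80% to 16/(16 + 1) = 94%, assuming equal retention in both arms. Elimination is then strong but not complete.

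**The case against.** The strongest reply is that nowhere does the article say that one person administers all three instruments. The blinding section uses the plural for assessors, and the sentence in *Data collection, entry and management* mixes singular and plural. The interviews have their own sample and guide, and no interviewer is named. Which member of staff handles which instrument is detail that an article often leaves to the full protocol. If different people do these tasks, the SSEQ assessor may stay blind.

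This stands as a limit on the consequence. A reader might infer that blinding is certainly lost at all three follow-ups; the documents do not support that. Loss at the immediate round depends on the order of the instruments, and loss at 4 and 12 weeks depends on the same person continuing. It does not remove the contradiction, because the blinding claim also covers the person who collects the arm-specific data, whoever that is.

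Other points on this side:
- The words limiting collection to the intervention group directly follow the qualitative data, so applying them to satisfaction is an inference. It is a safe one, given what the questionnaire asks.
- How the satisfaction questionnaire is completed is not stated. If participants fill it in alone, it need not inform the assessor; the interviews still would.
- *Proposed sample size* places the interviews loosely in the follow-up phase. Later interviews would not by themselves protect the 4- and 12-week SSEQ, because satisfaction is still collected immediately after the intervention.
- The SSEQ records the participant's own confidence, so an assessor has little room to score it differently. Prompting is the plausible route, and only if the SSEQ is taken by interview. The article gives a phone survey for baseline and no mode for follow-up.
- Participants are openly unmasked. On a self-rated outcome that is probably the larger source of bias, and assessor blinding does not touch it.

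**Conclusion.** The blinding statement is wrong as written: it covers data that cannot be collected without knowing the arm. This follows from the text alone.

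The effect on the SSEQ is conditional. On the plain reading, with one assessor continuing throughout, the 4- and 12-week rounds are not assessor-blinded, and the immediate round is not either unless the SSEQ comes first. With separate staff for the arm-specific instruments, the SSEQ could stay blinded, but the article does not provide for this.

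The importance is moderate. The SSEQ is a secondary outcome in a feasibility trial, retention and satisfaction do not depend on this blinding, and the limitations section already cautions about the small sample and the validity of outcomes. A reader might also infer that the SSEQ comparison would be free of bias if blinding were kept. The documents do not support that, because participants know their group and rate themselves.

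**What to change.** 1. In both sections, limit the blinding statement to the SSEQ.
2. Have the blinded assessor collect only the SSEQ, in both arms, at all three follow-ups, before any other instrument.
3. Have a different existing team member, who delivered no sessions, collect the satisfaction questionnaire and the interviews. The article does not identify such a person, so availability needs to be confirmed.
4. If that separation is not possible, do not describe the follow-up SSEQ as assessor-blinded.
5. In reports, describe the SSEQ as self-rated by unmasked participants.

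The cost is a short rewording and a reassignment of tasks within the team. It adds no participants, visits or instruments, and leaves collection of the satisfaction outcome otherwise unchanged.

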**Methods:**

Participants would be recruited at the University of Ghana Hospital and randomized into an intervention group and a control group. Participants aged ≥ 18 years, diagnosed of stroke at most 12months prior the recruitment and requiring moderate level of assistance would be considered for eligibility. Participants in the intervention group will receive individualized and comprehensive nurse-led rehabilitation therapies in physical, emotional, cognitive and nursing education domains for 6 months, in addition to treatment as usual (TAU). The control group will only receive treatment as usual. Follow-up evaluations will occur immediately, 30 days and 90 days after the intervention.

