### Eligibility criteria

Study participants will be considered for inclusion if they meet the following criteria:(1) is 18 years or above (2) diagnosed of a stroke with an onset of 1 week to 12 months prior the intervention (3) has FIM score of 55–100 (Level 3 moderate assistance) (4) total NIHSS score of 5–15 (moderate stroke). However, study participants would be excluded subject to these criteria: (1) has no access to a smartphone and standard internet connectivity (1.0 mgbs) (2) is unavailable for follow-up interviews (3) has a cognitive impairment (as documented in the patient’s medical records) that makes it difficult to comprehend the information provided and limits capacity to provide consent.

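### SSEQ has no common clock: follow-up is timed from an intervention that controls do not receive, and baseline is taken after allocation

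*Protocol article*

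**What the plan says.** **Follow-up.** The Abstract (Methods) states: "Follow-up evaluations will occur immediately, 30 days and 90 days after the intervention". The Intervention section agrees: "A follow-up evaluation would be performed at the end, 30- and 90-days after the intervention". Data collection, entry and management puts the first follow-up as soon as the intervention ends, with SSEQ in both groups, and the remaining two at "4 weeks and 12 weeks after the intervention respectively capturing stroke efficacy levels in both groups".

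**Baseline.** The same section describes two baseline occasions. Demographics, history, functional status, psychological functioning and cognitive capacity are gathered before randomisation. Self-efficacy is listed separately: it "would be collected before the first session of the intervention via phone survey". Randomization, allocation and blinding treats baseline self-efficacy as data gathered after allocation, by assessors who are blinded. It also says that participants are not blinded.

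**Control arm.** The same section describes the comparator as "control group (only treatment as usual"). No start or end date corresponding to the intervention is given for it.

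**Analysis.** Data analysis compares SSEQ levels between groups at the same follow-up points and examines change over time, with two-sided significance at p<0.05.

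**Onset window.** Eligibility criteria require a patient "diagnosed of a stroke with an onset of 1 week to 12 months prior the intervention". The Abstract has "diagnosed of stroke at most 12months prior the recruitment", with no lower limit.

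**The concern.** A between-arm comparison at a follow-up visit is clean only if that visit falls at the same time after randomisation in both arms. Here the SSEQ visits are dated from an event that happens in one arm only. In the intervention arm the event moves with the start and finish of the calls. In the control arm someone must choose a substitute date, and the article does not say which. If the two dates drift apart, arm is mixed with time since stroke and time since entry.

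The baseline has a second problem. SSEQ is a self-report of confidence. If it is taken after participants learn their arm, the answer can be affected by that knowledge, and blinding the assessor does not prevent this. It would then no longer be a clean pre-treatment value for judging comparability or change over time.

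At stake is the interpretability of the trial's one clinical outcome, which is meant to inform a larger study. The primary feasibility and satisfaction outcomes do not rest on matching SSEQ visit times between arms.

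**Working it through.** **1. Is there a clock for controls?**

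| SSEQ assessment | Stated reference | Exists in intervention arm | Exists in control arm |
|---|---|---|---|
| Baseline | before first session | yes | not stated |
| First follow-up | end of intervention | yes | not stated |
| Second and third follow-up | fixed time after intervention | yes | not stated |

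The article asks for SSEQ in both groups at all three follow-ups, so the gap affects each of them.

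**2. Is baseline SSEQ before or after allocation?** Data collection separates it from the data gathered before randomisation. The randomisation section places it after allocation and has the envelope opened as soon as consent is signed. Both point to after allocation.

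**3. Do the two statements of follow-up time agree?**
- 4 weeks × 7 = 28 days; 30 − 28 = 2 days.
- 12 weeks × 7 = 84 days; 90 − 84 = 6 days.

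They are two different schedules, but the gap is small and whichever applies would apply to both arms.

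**4. How firm is the end of the intervention?** The Intervention section gives 6 months: 365.25 / 2 = 182.6 days. In Table 1, physical rehabilitation has at most 48 sessions at two a week: 48 / 2 = 24 weeks = 168 days. Cognitive rehabilitation has 12 sessions, one every other week: 12 × 2 = 24 weeks. The two readings differ by 182.6 − 168 = 14.6 days.

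**5. Can the between-arm offset be computed?** Two inputs are missing: the lag L from randomisation to first session, and the rule for dating control visits. For illustration only, assume that control visits run from randomisation plus 182.6 days and intervention visits from the actual end of a course of length D. Then offset = (L + D) − 182.6, the same at every follow-up.

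| Assumed L (days) | D = 182.6 | D = 168 |
|---|---|---|
| 0 | 0 | −14.6 |
| 7 | +7.0 | −7.6 |
| 14 | +14.0 | −0.6 |
| 28 | +28.0 | +13.4 |

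If the team in practice dates both arms from randomisation, the planned offset is 0. The sign changes with the assumptions, so neither size nor direction follows from the documents.

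**6. The onset window.** The Abstract counts back from recruitment; Eligibility criteria count back from the intervention, which starts after randomisation. Taken literally, the second cannot be known exactly at screening and has no reference date for a control. Recruitment and screening nevertheless has the recruiting nurse complete eligibility screening, and the randomisation section randomises only patients already found eligible. The two wordings conflict, but the process described settles eligibility before allocation.

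**The case against.** The strongest reply is that parallel visits were plainly intended. The intervention has a nominal fixed length of 6 months, SSEQ is collected in both groups at the same phases, and the analysis compares groups at the same points. The Intervention section refers to a supplementary figure (S2 Fig), not shown here, that may set out the schedule, and a journal article condenses the full protocol. This stands in part: unequal timing is a risk, not an established fact. But the rule the article does state uses a reference that controls lack, and intent does not supply one.

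Other objections stand and limit the point:

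- A reader might infer that intervention visits will fall 7 to 28 days later than control visits. That needs an assumed lag, an assumed control clock and a full 6-month course. With a 24-week course and lags of 0 to 28 days, the range is about −15 to +13 days.
- A reader might infer that the onset criterion allows exclusions after randomisation that depend on arm. The article screens beforehand and describes no later re-check or exclusion.
- A reader might treat the 2- and 6-day discrepancies as a source of bias. They affect both arms alike.
- A reader might conclude that every time rule depends on the intervention. Most baseline data are gathered before randomisation, and the Abstract counts the onset window from recruitment.
- Fast recovery in the first weeks after stroke has little bearing on visits about 6 months after entry.

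Finally, the trial has 40 participants, and the Limitations section already warns that it may be too small to detect group differences.

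**Conclusion.** The point holds in a limited form. All SSEQ follow-ups are dated from an intervention that controls do not receive, and the visible text gives controls no counterpart. Visit times could therefore differ by arm, by an amount and in a direction that the documents do not determine. Baseline SSEQ is, on the article's own description, a self-report taken after allocation in unblinded participants; this part needs no assumption about timing.

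The two pairs of follow-up times (2 and 6 days apart) and the two reference dates for stroke onset are contradictions to reconcile, nothing more.

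Severity is low to moderate: one secondary outcome of a feasibility trial is affected, and the correction is cheap. The conclusion assumes that the supplementary schedule does not already define a control-arm clock. If it does, the main text still needs to say so, and the post-allocation baseline and the inconsistent wording remain.

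**What to change.** 1. Collect baseline SSEQ before randomisation, with the other baseline data.
2. Date the SSEQ assessments in both arms from randomisation: one at 6 months, then two at fixed intervals after it, with the same visit windows in both arms. Every participant has a randomisation date, so the planned offset becomes 0.
3. Use one of the two stated follow-up pairs (30 and 90 days, or 4 and 12 weeks) in the Abstract, Intervention and Data collection sections.
4. Reconcile the onset window in the Abstract and Eligibility criteria, including whether a lower limit applies, with a reference date that can be settled at the pre-randomisation screening.

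The cost is wording in four places, plus moving one questionnaire ahead of the envelope. Sample size and treatment are unchanged. One downside is real: an intervention participant who starts late may have sessions left at the 6-month SSEQ assessment. The satisfaction questionnaire is given only in that arm and needs no between-arm match, so it can stay tied to the end of sessions.
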